# Methods

## Overview

Prior to enrollment in the study, women will have two screening visits and an HIV medical evaluation at Chiang Rai Hospital to determine whether she is eligible to enroll in the study. In addition, women will ask their husband or steady male partner to be HIV tested to confirm that he is HIV-infected. He will need to sign an informed consent, because he may also be exposed to the study product, prior to enrollment. If eligible, women will be asked to provide informed consent prior to study enrollment. Women will participate in three study arms (two product, one no-product) and will be randomized to one of 6 possible study arm sequences (see section 5.5). Women will be asked to come to the clinic to begin each study arm approximately 3-5 days after the end of her menstrual period. Women using depo-provera will be followed on a 28 day schedule. At the first baseline visit (enrollment), a pelvic examination will be conducted, baseline CVL and vaginal swab samples will be collected for cervico-vaginal HIV viral load, and a colposcopic examination to assess the vaginal epithelium will be conducted. Immediately following the first examination and specimen collection, women who have been randomized to a product arm, will vaginally insert the first dose of the product, using the applicator as instructed. The participant will use the first product (or no product if in the no-product arm) in the sequence to which she is randomized. Approximately 15 minutes after she has inserted the product, the HIV CVL, swab and colposcopic examination will be repeated to assess acute effects of the product. If the arm of the sequence to which she is randomized is the arm in which no product is used, she will follow the same study visit schedule and will follow the same study steps as the other participants. Women will wait in the clinic 15 minutes, and then will be examined and have the HIV CVL, swab, and colposcopic examination repeated. Women who are assigned to a product arm will apply the product at home once daily for a total of seven days (Table 1). On study day 7 (following 7 days of daily product use), participants (irregardless of whether they are in a product or no product arm) will return to the clinic for another pelvic examination when cervico-vaginal HIV viral load measurements (using CVL and vaginal swabs) and colposcopic examinations will be repeated. At the second follow-up visit on day 14 (7 days after discontinuing product use), participants (whether they are in a product or no product arm) will return to the clinic for another pelvic examination when cervico-vaginal HIV viral load measurements (using CVL and vaginal swabs) will be collected. Women will then return to the clinic approximately 3-5 days after the end of the next menstrual period (day 28 for women using depo-provera) and, at that time, after a three week washout period, will begin the next study arm in her study arm sequence (See Table 1).

## Design

Randomized, controlled, double-blind, three arm, cross-over trial

## Study products

The Population Council will supply Carraguard and its matching placebo in boxes of pre-packaged tube-shaped Microlax applicators which contain 7 mL of the product and dispense 4 mL of the product upon self-administration. The product and placebo will be manufactured according to the Population Council’s specifications and in accordance with FDA guidelines. Shipping of study product to the study site will occur according to a shipping Standard Operating Procedure (SOP). Shipments are labeled with FDA-mandated labels, indicating that they contain a ANew Drug Limited by Federal Law (USA)” and are for AInvestigational Use Only.@ They also contain detailed information about the contents of the shipment and relevant contact information.

**Composition of Carraguard**

Carraguard is the Population Council’s leading microbicide candidate. The active pharmaceutical ingredient (API) in Carraguard is a sulfated polysaccharide mixture of mostly *lambda-* with a smaller amount of *kappa-*carrageenan (FMC, PDR98-15), both derived from the seaweed species *Chondrus crispus*. The molecular weight is between 150,000 and 10 million. In the Carraguard gel formulation, the carrageenan mixture is dissolved in purified water with 0.1% p-hydroxybenzoic methyl ester added as a preservative. Phosphate-buffered saline (PBS) and hydrochloric acid are used to adjust the pH to 7.

## Study arms

- Carraguard (A)
- Placebo (Methyl cellulose gel) (B):
- No product (C)

## Study arm sequences

- A-B-C (1)
- A-C-B (2)
- B-A-C (3)
- B-C-A (4)
- C-B-A (5)
- C-A-B (6)

## Sample size

The two primary hypotheses in this study are that Carraguard is 1) different from placebo and 2) different from no product. A primary outcome is cervico-vaginal HIV shedding measured after 7 days of daily product use. The power calculation is based on ensuring adequate power for testing these two hypotheses with this outcome with an overall significance level of 0.05. We used a 3x3 Williams design to determine power/sample size (see graph below). The Williams design is a cross-over design balanced for first carry-over effects when testing products used in sequence and will provide minimum variance unbiased estimates for the treatment effect comparisons in the presence of first order carry-over effects. It is not known whether the washout period used in this study design will be sufficient to assume no carry-over effects, hence a Williams design was employed to ensure unbiased minimum variance estimates. If there are no carry-over effects (i.e. the power will be higher than indicated) the power calculations for this design are conservative.

The null hypotheses for these primary hypotheses are: 1) No difference between Carraguard and no product and 2) no difference between Carraguard and placebo.

In order to carry out the power calculations the within subject variability needs to be specified, as well as an effect size, defined here as the average difference between a pair of treatments. Estimates of the underlying variability of genital tract HIV shedding are based on preliminary data from the CDC laboratory studies (unpublished), where the vaginal viral load was measured weekly throughout the menstrual cycle (i.e. for three weeks after menses) for 45 HIV-infected women. Based on a one-way repeated measures ANOVA, the within standard deviation of cervico-vaginal HIV shedding on the log scale was estimated as 0.66.

The following plot shows the power to detect a statistically significant difference between a pair of treatments for varying effect sizes with an overall sample size of 30 or 50, at a significance level of 0.025 (based on the Bonferroni adjustment for the two planned pairwise comparisons, for an overall Type I error rate of 0.05). A horizontal line indicates 80% power. The effect size is based on the difference between a pair of treatment means on the log scale. Thus the plot shows that with a sample size of 30 and a within standard deviation of 0.6, there is at least 80% power to detect a difference between a pair of treatment means (on the log scale) of 0.55 or higher. On the other hand, with a sample size of 50 and a standard deviation of 0.6, there is at least 80% power to detect a difference between a pair of treatment means (on the log scale) of 0.43 or higher. The estimates of power would be higher if no carryover effect truly exists. Sixty women will be enrolled to account for participants lost to follow-up and participants who may start antiretroviral therapy and so there is an equal number of women in each study sequence.

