**Study plan**

Women will be screened for eligibility, which will include two screening visits, HIV, and tuberculosis testing, and an HIV clinical evaluation. If a woman has a husband or steady sex partner, he will need to come to the clinic for HIV testing to confirm that he is HIV-infected (and therefore not at risk for HIV infection related to the woman’s study participation) and to provide informed consent, because he may also be exposed to the study product, prior to her enrollment. Informed consent will be obtained. This study includes three study arms: Carraguard, placebo, and a no product arm. During the study, each woman will participate in each study arm, and she will be randomized to one of six study arm sequences (see section 5.5). At the enrollment visit, a pelvic examination will be conducted. During the examination, a baseline cervico-vaginal lavage (CVL) HIV sample and vaginal swab sample will be collected to quantify genital tract HIV, and a baseline colposcopic examination will be conducted to evaluate the mucosal epithelium. After the pelvic examination is conducted, the woman will be randomized to a study arm sequence. When receives a product, she will insert the gel vaginally as directed while still at the clinic. The participant and the research staff will be blinded regarding which gel the participant is using. Fifteen minutes after the product is inserted, a second pelvic examination will be conducted, 2 CVLs and vaginal swab samples will be collected, and a repeat colposcopic examination will be conducted to assess any acute effects of product exposure. If it is determined that one CVL is adequate to assess acute effects, only one CVL will be collected after the gel application at each baseline visit for the duration of the study. Participants who do not use a product will also undergo a second pelvic examination with CVL, vaginal swab and colposcopy at 15 minutes. During each study arm, the participant will use the designated product (or no product) for one week, beginning 3-5 days after the end of her menstrual period. She will have a total of two follow-up visits at day 7 and day 14 (1 and 8 days after discontinuing product use). Women and their partners will be counseled regarding the use of condoms and will be given condoms at no cost, to prevent transmission of different viral strains between partners. Women will be asked to return to the clinic for a pelvic examination with CVL and vaginal swab sample collection for HIV and colposcopy. On day 14 (~7 days after discontinuing product use), another pelvic examination with CVL and vaginal swab for HIV will be conducted. Women will then be asked to wait until 3-5 days after the end of the next menstrual cycle to return to clinic for the first visit in the next arm of their study arm sequence baseline study visit). Data from the baseline study visit will also be used for analysis of day 28 delayed effects or potential carry-over effects from the previous arm. A questionnaire regarding product use, acceptability, and adherence will be administered at the first follow-up visit (day 7) of each product arm. All women will participate in each study arm. The three study visits and data collection described above will be repeated for each of the 3 study arms.

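### Bonferroni for the two primary comparisons is valid, but Holm's step-down holds the same overall 0.05 and, with 50 women and two equal real effects, adds about 4-5 points of power per comparison and 9-10 points for both

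*Protocol*

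**What the plan says.** All that the protocol says on multiplicity stands under Sample size. It declares two primary hypotheses: "The two primary hypotheses in this study are that Carraguard is 1) different from placebo and 2) different from no product". It sets the error rate for "testing these two hypotheses with this outcome with an overall significance level of 0.05". The power plot uses 0.025 for each comparison, "based on the Bonferroni adjustment for the two planned pairwise comparisons".

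The design behind the calculation is also stated there ("We used a 3x3 Williams design to determine power/sample size"), and under Study plan each woman follows one of six sequences ("she will be randomized to one of six study arm sequences"). The detectable differences are quoted at a within-subject SD of 0.6: at least 80% power for 0.55 with 30 women and for 0.43 with 50. The preliminary data gave a slightly larger SD: "the within standard deviation of cervico-vaginal HIV shedding on the log scale was estimated as 0.66". Sixty women are to be enrolled, to allow for loss to follow-up and for women who start antiretroviral therapy.

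The Data analysis section gives the mixed model, and has the carry-over term removed if no carry-over is found. It names no multiplicity procedure.

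**The concern.** Plain Bonferroni holds each comparison to 0.025 whatever the other shows. Holm relaxes the second test to 0.05 once the first has succeeded. It rejects everything that Bonferroni rejects and sometimes more, at the same familywise error.

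Both comparisons are declared primary and share the Carraguard arm, so a product that shifts shedding may well differ from both controls. That is the situation in which Bonferroni loses most. What is at stake is some power for the second comparison. The validity of the test and the correctness of the sample size are not in question.

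**Working it through.** **Inputs from the protocol.** Two comparisons; overall alpha 0.05, read as two-sided because the hypotheses are of difference; 0.025 each; six sequences in three periods; a model with subject, period, treatment and first-order carry-over; SD 0.6 or 0.66; 30 women with a difference of 0.55; 50 women with a difference of 0.43.

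**Assumptions made here.** Both true effects are equal and in the same direction unless stated otherwise. Sequences are treated as balanced.

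**Variance.** Least squares on the six-sequence design gives, for a treatment difference,

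- with carry-over: variance = 2.5 × SD² / N, residual df = 3N − N − 2 − 2 − 2 = 2N − 6;
- without carry-over: variance = 2.0 × SD² / N.

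The two contrasts that share Carraguard have correlation 1.25 / 2.5 = 0.5.

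**The plan's own figures first** (noncentral t, two-sided 0.025, SD 0.6, carry-over in the model):

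- N = 30: SE = 0.6 × √(2.5/30) = 0.173; 0.55 / 0.173 = 3.18; df 54; power 80.5%.
- N = 50: SE = 0.6 × √(2.5/50) = 0.134; 0.43 / 0.134 = 3.205; df 94; power 82.1%. With 48 women (8 per sequence) it is 80.4%.

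Both agree with the stated minimum of 80%.

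**Bonferroni against Holm** (simulated bivariate t, correlation 0.5, carry-over in the model; gains taken before rounding, last digit good to about 0.1):

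| N, difference, SD | Per comparison | Gain | Both | Gain |
|---|---|---|---|---|
| 30, 0.55, 0.6 | 80.5% → 85.2% | 4.7 | 69.7% → 79.0% | 9.4 |
| 50, 0.43, 0.6 | 82.1% → 86.5% | 4.4 | 71.8% → 80.6% | 8.8 |
| 30, 0.55, 0.66 | 71.8% → 77.2% | 5.3 | 58.3% → 69.0% | 10.7 |
| 50, 0.43, 0.66 | 73.7% → 78.8% | 5.2 | 60.5% → 70.9% | 10.4 |

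A hand check is possible, because power for both equals the sum of the two separate powers minus the chance of at least one rejection, and that chance is the same under both methods. In the second row it is 92.4%. Bonferroni: 82.1 + 82.1 − 92.4 = 71.8. Holm: 86.5 + 86.5 − 92.4 = 80.6. With equal effects the gain for both is therefore twice the gain per comparison.

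**Where the gain shrinks** (difference 0.43, points per comparison / for both):

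| Setting | SD 0.6 | SD 0.66 |
|---|---|---|
| N = 60, carry-over in model | 3.3 / 6.6 | 4.4 / 8.8 |
| N = 50, no carry-over term | 3.1 / 6.1 | 4.2 / 8.4 |
| N = 60, no carry-over term | 1.9 / 3.8 | 3.1 / 6.2 |

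**Unequal effects** (N = 50, SD 0.6, carry-over in the model). If only one effect is real, its power rises by about 0.2 points. If the second effect is half the first, the larger gains about 0.5 points and the smaller goes from 25.4% to 34.6%.

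**Error rate.** With no effect in either comparison, the simulated chance of any false rejection is 4.6% under both procedures.

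**The case against.** The strongest answer is that nothing here is wrong. Two tests at 0.025 respect an overall 0.05, the quoted power reproduces, and Bonferroni pairs naturally with simultaneous 97.5% intervals. The sentence at issue describes a power calculation, and powering at 0.025 is compatible with analysing by Holm. An SAP that is not at hand may already name the test procedure. All of this stands, and it is why the point is an optional improvement and not a defect. It is still worth raising, because Bonferroni is the only multiplicity rule that the protocol gives.

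A reader might infer four stronger things, none of which the documents support:

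- *That Bonferroni gives up power for nothing.* Under Holm, a second comparison with a p-value between 0.025 and 0.05 is significant although its 97.5% interval includes zero. That is a small but real cost.
- *That Holm makes good the gap between the two SDs.* The detectable differences are quoted "with a sample size of 30 and a within standard deviation of 0.6" (and likewise with 50), while the estimate was 0.66. At N = 50, power per comparison falls from 82.1% to 73.7%, a loss of 8.5 points before rounding. Holm returns 5.2 of them, about 60%, and leaves power below 80%.
- *That the trial needs success on both comparisons.* The protocol states two separate hypotheses under one error rate and does not require both. If it did, each could be tested at 0.05 without adjustment, and Holm would not be the natural remedy.
- *That 97.5% intervals are already planned.* The protocol does not mention them.

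**Conclusion.** The point holds as a cheap gain in efficiency. Holm controls the same overall 0.05 under any dependence and never rejects less than Bonferroni. For the 50-woman case the gain is about 4-5 points per comparison and 9-10 points for both. The 30-woman case is similar, reaching 10.7 points for both at SD 0.66.

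These sizes rest on both effects being real and equal and on carry-over staying in the model. More evaluable women, or removal of the carry-over term, reduces them. With both changes they are about 2-3 and 4-6 points. With only one real effect almost nothing is gained, though nothing is lost. The chance of finding at least one difference is identical under the two methods.

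**What to change.** State before unblinding, in the Data analysis section or the SAP, that the smaller of the two primary p-values is tested at 0.025 and that, only if it is rejected, the other is tested at 0.05. Leave the Sample size figures at 0.025 and describe them as conservative for this procedure. If 97.5% simultaneous intervals are reported, add a note that a second comparison significant only at 0.05 may have an interval that includes zero.

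The change costs one sentence and that note. Enrolment, visits and the model stay as they are. If the SAP already specifies a step-down test, only the protocol wording needs to be aligned.

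### The protocol's 80% power statements use a within-woman SD of 0.6 without explanation, although its own estimate is 0.66; at 0.66, with carry-over in the model, power is about 72% and 74%

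*Protocol*

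**What the plan says.** All of this is in the protocol, Methods, Sample size.

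- **Hypotheses and error rate.** "The two primary hypotheses in this study are that Carraguard is 1) different from placebo and 2) different from no product". The calculation is made "with an overall significance level of 0.05", and each comparison is tested "at a significance level of 0.025 (based on the Bonferroni adjustment for the two planned pairwise comparisons".
- **Design behind the power.** "We used a 3x3 Williams design to determine power/sample size". The protocol chose it because it does not know whether the washout removes carry-over. It adds: "The estimates of power would be higher if no carryover effect truly exists".
- **Variability.** The section says a within-subject variability has to be specified. From unpublished weekly measurements on 45 HIV-infected women, "the within standard deviation of cervico-vaginal HIV shedding on the log scale was estimated as 0.66". No other estimate is given.
- **Power conclusions.** Reading from a plot, the text says "with a sample size of 30 and a within standard deviation of 0.6, there is at least 80% power" for a difference of 0.55 or more, and "with a sample size of 50 and a standard deviation of 0.6, there is at least 80% power" for 0.43 or more.
- **Enrolment.** Sixty women are enrolled, to cover losses to follow-up and antiretroviral starts and to fill the six sequences equally. No dropout rate is stated.

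**The concern.** The protocol says the calculation needs a within-woman SD, supplies 0.66, and then draws both power conclusions at 0.6. Nothing in the text links the two values. Rounding does not explain it, since 0.66 to one decimal is 0.7. The change is in the favourable direction: a smaller SD gives more power.

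This matters because shedding after 7 days of use is the outcome on which the sample size rests. A reader who takes 0.66 as the planning value and 80% as the planned power will credit the trial with more sensitivity than the protocol's own estimate supports under the model it chose for the calculation.

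**Working it through.** **Inputs.** Within-woman SD 0.6 (power text) and 0.66 (protocol's estimate); N = 30 with difference 0.55 and N = 50 with difference 0.43; level 0.025 per comparison; the six sequences in Study arm sequences. The test is taken as two-sided because the hypotheses are worded as differences, and SD and difference are taken on the same log scale. The protocol states neither point.

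**Variance of a treatment difference.** A least-squares design matrix was built for the six sequences, with subject level (represented by sequence), period, treatment and first-order carry-over. It gives

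- with carry-over: Var = 2.5 × SD² / N
- without carry-over: Var = 2.0 × SD² / N

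**Power.** Noncentrality = difference / √Var. Power is the noncentral-t probability of exceeding the upper 0.0125 point of t, with 2N − 6 degrees of freedom with carry-over and 2N − 4 without. The far tail is negligible.

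**Step 1: reproduce the protocol at SD 0.6, with carry-over.**

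- N = 30: SE = 0.6 × √(2.5/30) = 0.1732; 0.55/0.1732 = 3.175; critical t (54 df) = 2.306; power 80.5%. Power reaches 80% at a difference of 0.547.
- N = 50: SE = 0.6 × √(2.5/50) = 0.1342; 0.43/0.1342 = 3.205; critical t (94 df) = 2.278; power 82.1%. Power reaches 80% at 0.419. Since 50 does not divide by six, 48 women (8 per sequence) may have been used: that gives 80.4%, with 80% at 0.428, which matches the stated 0.43 closely.

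Both statements of at least 80% are reproduced, so 0.6 was the value used and is not a misprint of 0.66.

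**Step 2: the same calculation at SD 0.66.**

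- N = 30: SE = 0.66 × √(2.5/30) = 0.1905; 0.55/0.1905 = 2.887; power 71.8%.
- N = 50: SE = 0.66 × √(2.5/50) = 0.1476; 0.43/0.1476 = 2.914; power 73.7%.

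The normal approximation agrees: Φ(2.887 − 2.241) = 74.1% and Φ(2.914 − 2.241) = 74.9%.

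**Step 3: drop the carry-over term, SD 0.66.**

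- N = 30: SE = 0.66 × √(2/30) = 0.1704; 0.55/0.1704 = 3.227; power 81.9%.
- N = 50: SE = 0.66 × √(2/50) = 0.1320; 0.43/0.1320 = 3.258; power 83.5%.

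**Step 4: differences detectable with 80% power, carry-over in the model.**

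| N evaluable | SD 0.6 | SD 0.66 |
|---|---|---|
| 30 | 0.547 | 0.601 |
| 50 | 0.419 | 0.461 |
| 60 | 0.382 | 0.420 |

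Each entry grows by 0.66/0.6 = 1.10. At SD 0.66, 80% power needs 36 evaluable women for 0.55 and 58 for 0.43. With all 60 evaluable, SE = 0.66 × √(2.5/60) = 0.1347; 0.43/0.1347 = 3.192; power for 0.43 is 82.0%.

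**The case against.** The strongest reply is that nothing stated is false. Each sentence names its SD, and at 0.6 the figures are right. This stands: the defect is an unexplained input, not a miscalculation.

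The text also reads its values from a plot that could not be seen here. It may carry curves for other SDs, so one cannot say that the protocol gives nothing at 0.66. One can say that the available text draws its conclusions only at 0.6 and does not connect that value with the estimate.

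Third, the calculation is conservative if there is no carry-over, and the Data analysis section plans to drop the term in that case. Power at 0.66 is then about 82% and 83%. This also stands, but the protocol presents the gain as additional to the quoted power; at 0.66 it is largely used up in getting back above 80%. Similarly, 60 evaluable women would give 82% for 0.43, but the protocol assigns the women beyond 50 to losses and antiretroviral starts.

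Two stronger readings are tempting, and the documents support neither.

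- *That 0.66 is itself probably too low, because the preliminary data covered one menstrual cycle and the trial spans several.* Between-cycle variation could raise the SD, but sampling at a roughly fixed cycle phase and fitting period effects could lower it. No figure is given for either.
- *That a null result would be taken to exclude 0.43 or 0.55.* The protocol plans model-based estimates of treatment effects, names no target difference, and attaches no decision rule to these values.

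**Conclusion.** The point holds as an unexplained and favourable choice of SD in the power statements. At the protocol's own 0.66, with carry-over modelled, the quoted differences have about 72% power (30 women) and 74% (50 women) instead of at least 80%. Like for like, the detectable difference is 10% larger. Without the carry-over term, power stays above 80% in both cases.

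It would be too strong to infer that the protocol's arithmetic is wrong or that the trial is too small. The quoted figures are right for 0.6, and the 60 women planned remain a workable number. The result assumes a two-sided test and one log scale for SD and difference; the reproduction of the protocol's figures supports the two-sided level of 0.025. Severity: should be fixed.

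**What to change.** In Sample size, restate the power sentences at SD 0.66 with carry-over in the model: 80% power for a difference of 0.60 with 30 women, 0.46 with 50, and 0.42 with 60 if all are evaluable. Alternatively, keep 0.6 and give the reason for preferring it to the estimate of 0.66. If the plot already has a curve at or near 0.66, refer to it in the text.

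This is a change of text only. Enrolment stays at 60, and design and analysis are untouched. The cost is a stated detectable difference about 10% larger.
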